## 4. Rationale

Evidence suggests that timely and effective management can improve long-term outcomes in patients with PsA. The factors influencing management decisions in PsA are not well understood. In the field of diabetes mellitus, the interactions of patient, physician and systemic factors were found to have implications for the implementation of a diabetes management model (39).

Early diagnosis of PsA is the first and crucial step in effective management of PsA, The detection of inflammatory musculoskeletal symptoms drives PsA diagnosis. The clinical patterns of PsA are heterogeneous and may vary in an individual patient over time, which renders recognition of the disease by non-rheumatologists and patients challenging, leading to a delay in diagnosis and worse long term outcomes. Therefore, the time of musculoskeletal symptoms onset is selected in this study as the anchor date for describing different management steps in patients with PsA. In order to assess this aspect in the overall PsA population both patients with established and suspected PsA diagnosis will be asked to participate in the study. Medical care of PsA patients are provided by various clinical specialties, such as rheumatologists, dermatologists, other specialists and primary care practices. In order to describe the overall PsA population, which includes patients with mild disease that are not consulting physicians with rheumatology or dermatology expertise, the study aims to include PsA patients from all specialties providing medical care.

This study is expected to provide important insights into the factors influencing management of PsA, which may aid planning improvements in the standards of care in this chronic systemic disease.

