### Secondary objectives:

- To explore the association between the timing of various management steps and current disease activity and burden in patients with a confirmed PsA diagnosis
- To describe the disease characteristics and comorbidities of patients whose suspected PsA diagnosis is not confirmed through a current routine rheumatological and dermatological assessment

This is an observational study. It is not designed to identify or quantify a safety hazard relating to an authorized medicinal product.

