### 8.2. Plan for Statistical Analysis

Only patients with a confirmed diagnosis of PsA will be eligible for statistical analysis. The exact definition of the analysis populations will be detailed in a separate statistical analysis plan.

Collected data will be summarized by descriptive statistics. Quantitative variables will be reported as absolute N, mean, standard deviation, median, 1st and 3rd quartiles and minimum and maximum. Qualitative variables will be reported as absolute and relative frequency distributions.

Research outcomes of primary and secondary interest will be analyzed using descriptive statistics overall and in subgroups defined by explanatory variables (disease severity perception by patients and physicians and clinical specialty). Effects will be estimated depending on the scale of the endpoint by use of mean differences or ORs with respective 95% confidence interval. The effect estimates will be calculated from simple regression

Confidential Information

No use or disclosure outside AbbVie is permitted without prior written authorization from AbbVie

models run separately for each of the explanatory variables and thereafter in multiple regression models with variable selection to identify and assess important explanatory variables. Depending on the scale of the dependent variable, linear or logistic models will be used.

PsA clinical manifestation and disease burden will be analyzed using descriptive statistics. Regression analyses will be done as described above, using time from symptom onset to PsA diagnosis, time from PsA diagnosis to first csDMARD, first bDMARD and from first csDMARD to first bDMAD as explanatory variables.

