### 8.3. Sample Size Calculation

The factor that is most likely to influence the PsA management components of interest is clinical specialty. However, there is no scientific basis currently to judge the effect size.

So this will be an exploratory study and objectives are exploratory in nature (non-confirmatory) and no adjustment for multiplicity will be made.

With 400 evaluable patients in rheum and dermatology sites, the study has 90% power to detect a difference in means between the two specialties with a two-sample t-test at a significance level of 5% assuming an effect size of 0.229. With 400 evaluable patients in rheum or dermatology sites and 200 evaluable patients in non-rheum/non-dermatology sites, the study has 90% power to detect a difference in means between rheum vs. non-rheum/non-dermatology or dermatology vs. non-rheum/non-dermatology, respectively, with a two-sample t-test at a significance level of 5% assuming an effect size of 0.281.

The estimated drop-out rates due to non-confirmed PsA diagnosis are 10% in rheum, 15% in dermatology and 25% in non-rheum/non-dermatology sites. Hence, a total number of approximately 1200 patients (450:480:270 in rheum:dermatology:non-dermatology/non-rheum, respectively) has to be recruited in order to achieve 1000 evaluable patients (400:400:200 in rheum:dermatology:non-dermatology/non-rheum, respectively).

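### In the secondary regressions, variable selection among time-ordered intervals leaves open whether the diagnostic-delay coefficient is a total association or one net of later treatment timing

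*Protocol*

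**What the plan says.** The secondary objective in Protocol section 5 is "To explore the association between the timing of various management steps and current disease activity and burden" in patients with confirmed PsA. Section 8.2 serves it with regressions of clinical manifestation and burden on four intervals: "using time from symptom onset to PsA diagnosis, time from PsA diagnosis to first csDMARD, first bDMARD and from first csDMARD to first bDMAD".

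The method is carried over from the preceding paragraph of the same section: "Regression analyses will be done as described above". That paragraph prescribes "models run separately for each of the explanatory variables and thereafter in multiple regression models with variable selection". The purpose it gives for the multiple stage is to find and evaluate the explanatory variables that matter.

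Section 4 states that "Early diagnosis of PsA is the first and crucial step in effective management of PsA". Section 8.3 adds that "objectives are exploratory in nature (non-confirmatory) and no adjustment for multiplicity will be made". Section 8.2 defers the definition of the analysis populations to the SAP. It names neither an order among the intervals nor a model that answers the objective for each step.

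**The concern.** The intervals are successive steps: symptom onset to diagnosis, diagnosis to first csDMARD, first csDMARD to first bDMARD. Diagnosis to first bDMARD spans the last two. A later interval may lie on the path from late diagnosis to present burden, and an earlier one may confound the later ones. The multiple stage treats them all as interchangeable candidates and lets fit decide.

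Two things can then go wrong:

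- Diagnostic delay may be judged after conditioning on what followed diagnosis.
- A treatment interval may be judged without the delay that preceded it.

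Selection is repeated for each outcome (joint counts, skin scores, HAQ-DI, SF-12, WPAI, DLQI), so coefficients with the same label may answer different questions. A selected model without diagnostic delay could be read as showing that only drug timing matters. The study aims to inform standards of care and starts from the importance of early diagnosis, so that reading would carry weight.

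**Working it through.** **Inputs.** The four intervals and the two-stage procedure come from sections 8.1 and 8.2. The documents do not give the effect of diagnostic delay on a later interval (a), the effect of that interval on burden (b), or the direct association of diagnostic delay with burden (d). All three are assumed below, in SD units.

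**The plan's own figures.** None is stated for the secondary regression. The sample-size figures in section 8.3 concern the specialty comparison, and they reproduce. With a two-sided 5% t-test (sidedness assumed), 400 against 400 patients "assuming an effect size of 0.229" gives 89.9% power, and 400 against 200 at 0.281 gives 90.0%. Recruitment is 400/0.90 = 445, 400/0.85 = 471 and 200/0.75 = 267, total 1183, against about 1200 stated. These figures do not bear on the present point.

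**What each possible selected model estimates.**

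| Intervals kept | Onset-to-diagnosis coefficient | Later-step coefficient |
|---|---|---|
| Onset to diagnosis only | Total (unadjusted) association | Not estimated |
| Onset to diagnosis + a later interval | Net of that later interval | Adjusted for the earlier delay |
| A later interval only | Not estimated | Not adjusted for the earlier delay |

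**Size for diagnostic delay.** In a linear model, total = d + a × b and the adjusted coefficient = d, so adjusted − total = −(a × b). With d = 0.30:

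| a | b | Total = 0.30 + a × b | Adjusted | Adjusted against total |
|---|---|---|---|---|
| +0.5 | +0.3 | 0.45 | 0.30 | smaller |
| −0.5 | −0.3 | 0.45 | 0.30 | smaller |
| 0 | ±0.3 | 0.30 | 0.30 | equal |
| −0.5 | +0.3 | 0.15 | 0.30 | larger |
| +0.5 | −0.3 | 0.15 | 0.30 | larger |

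A simulation with 200,000 records agreed with these values to within about 0.005. The regression on diagnostic delay alone returned the total in every case.

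With smaller assumed slopes (d = 0.10, b = 0.15, correlation r = 0.3 between the delays), the total is 0.10 + 0.3 × 0.15 = 0.145. The adjusted value of 0.10 is lower by 0.045/0.145 = 31%. Over r = 0.2 to 0.4, d = 0.05 to 0.10 and b = 0.10 to 0.15, the share runs from 0.02/0.12 = 17% to 0.06/0.11 = 55%. These percentages illustrate the all-positive case only. With r = −0.3 the total is 0.10 − 0.045 = 0.055, and the adjusted 0.10 lies above it.

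**Size for a later step.** If the earlier delay is left out, the later step's slope becomes b + r × d. With r = 0.3 and d = 0.10 to 0.15, the added part is 0.03 to 0.045. With negative r it is subtracted instead.

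**Not the same as linear dependence.** Where both drug types were given and all dates are known, with the csDMARD first, diagnosis-to-bDMARD is the sum of the other two treatment intervals, so the three cannot all enter one linear model. Removing one of them leaves the present question untouched.

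**The case against.** The strongest reply is that the total association is already planned. The first stage regresses each outcome on onset-to-diagnosis alone, which is the model needed for that step. This stands: a reader might infer that the study can estimate diagnostic delay only net of its consequences, and section 8.2 does not support that. What the plan lacks is a statement that this simple model is the answer for diagnostic delay. As written, the simple stage is a forerunner to the stage that sorts the important variables.

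A second reply is that the later intervals are only candidates and may not be kept. That is correct, so the adjustment is possible rather than certain. It does not rescue the rule, because selection by fit makes the adjustment set vary between outcomes and can remove the earlier delay from a model for a later step.

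A third reply concerns direction. A reader might infer that the multiple model understates the association of late diagnosis with burden. The documents do not show this. The later intervals are counted from diagnosis or from the first csDMARD, so they do not contain the diagnostic delay, and late-diagnosed patients could be treated sooner after diagnosis. The Introduction describes escalation when a disease target is missed, so a short interval may also mark worse disease. The reply stands in full.

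Finally, the objective is an exploratory association, and mutual adjustment is a legitimate way to ask which steps are independently associated with burden. That is fair, and it limits the weight of the point. Exploratory status waives multiplicity adjustment, but a reader still has to know what each coefficient measures.

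**Conclusion.** The point holds as one of interpretation and model choice. Under the stated rule, the onset-to-diagnosis coefficient from the multiple model is the total association only if no later interval is kept, or if those kept carry none of it. A later step is adjusted for the earlier delay only if selection happens to keep that delay.

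No direction or size of bias can be claimed. The adjusted coefficient falls below the total only if a × b has the same sign as the direct association; otherwise it is equal or larger. Over the assumed range, total minus adjusted runs from −0.15 to +0.15 SD. The 17 to 55% figures rest on positive signs throughout. Nor can a loss of power be quantified, because the documents do not say how many patients will have each interval and the SAP may settle how missing intervals are handled.

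The algebra assumes linear relations. The simple model's total association remains open to confounding by factors other than the intervals. This is a cheap improvement to a stated rule and does not threaten the primary objective.

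**What to change.** For the secondary objective, replace variable selection among the intervals with pre-set time-ordered models for each outcome:

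1. Onset-to-diagnosis with no later interval. This is the simple model already planned, now designated as the answer for diagnostic delay.
2. Diagnosis-to-csDMARD with onset-to-diagnosis forced in.
3. csDMARD-to-bDMARD with both earlier intervals forced in.

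Interpret only the latest step's coefficient in each model. If a joint model is also shown, label its onset-to-diagnosis coefficient as the association not explained by later treatment timing. Diagnosis-to-bDMARD should not enter model 3 beside its two components. If it is reported on its own, the same rule applies: onset-to-diagnosis forced in, neither component included.

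The cost is a change of wording in the protocol or SAP and three short models per outcome, with no new data. The downside is that the three coefficients come from different patient sets, since fewer patients have the later intervals. Each should be reported with its own patient number and not compared as if drawn from one population.

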### 8.3. Sample Size Calculation

The factor that is most likely to influence the PsA management components of interest is clinical specialty. However, there is no scientific basis currently to judge the effect size.

So this will be an exploratory study and objectives are exploratory in nature (non-confirmatory) and no adjustment for multiplicity will be made.

With 400 evaluable patients in rheum and dermatology sites, the study has 90% power to detect a difference in means between the two specialties with a two-sample t-test at a significance level of 5% assuming an effect size of 0.229. With 400 evaluable patients in rheum or dermatology sites and 200 evaluable patients in non-rheum/non-dermatology sites, the study has 90% power to detect a difference in means between rheum vs. non-rheum/non-dermatology or dermatology vs. non-rheum/non-dermatology, respectively, with a two-sample t-test at a significance level of 5% assuming an effect size of 0.281.

The estimated drop-out rates due to non-confirmed PsA diagnosis are 10% in rheum, 15% in dermatology and 25% in non-rheum/non-dermatology sites. Hence, a total number of approximately 1200 patients (450:480:270 in rheum:dermatology:non-dermatology/non-rheum, respectively) has to be recruited in order to achieve 1000 evaluable patients (400:400:200 in rheum:dermatology:non-dermatology/non-rheum, respectively).

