## 5. Study Objectives

### Primary objective:

- To evaluate the association between the clinical specialty setting and time from inflammatory musculoskeletal symptom onset to PsA diagnose and to different management steps in patients with a confirmed PsA diagnosis

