## 6. Observational Plan

### 6.1. Study Conduct

This study will be performed in a cross-sectional, observational, multi-country, multi-center format in approximately 15 countries across different geographical regions.

The study population will consist of patients who are 18 years or older, have been diagnosed with suspected or established Psoriatic Arthritis (PsA) and attending a routine clinical visit at the participating clinical sites. Suspected PsA diagnosis is based on clinical judgement of the recruiting physician.

In order to describe the overall PsA population, all specialties providing medical care of PsA patients will be included. The study will be conducted in a convenience sample recruited at rheumatology, dermatology, other specialist and primary care practices. These are providing medical care for 37-38% (rheumatology), 22-28% (dermatology), 7-12% (other specialists) and 28% (primary care practices) of PsA patients, respectively, depending on the country (38). Other specialties may include orthopedists, ophthalmologists, physiatrists and podiatrists according to the standard practice in the respective country (34). For the sake of convenience, other specialist and primary care practices will be referred to as non-rheum/non-derm sites in this research plan.

Patients with a suspected or an established diagnosis of PsA scheduled for routine visit at the recruiting site (dermatologist, rheumatologist or a non-rheum/non-derm site) can be offered the opportunity to participate in the study. Patients will be recruited on a consecutive basis. Patient characteristics, relevant co-morbidities and medical history, disease, diagnostic and treatment data will be documented in the Data Recording Form (DRFs) for data available in the medical charts.

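### The stated 90% power for the specialty comparisons holds only if patients at the same site are uncorrelated, although specialty varies only between sites

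*Protocol*

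**What the plan says.** The primary objective (Protocol section 5) is "To evaluate the association between the clinical specialty setting and time from inflammatory musculoskeletal symptom onset to PsA diagnose", and to later management steps. Section 6.1 describes the design: "This study will be performed in a cross-sectional, observational, multi-country, multi-center format in approximately 15 countries across different geographical regions". On sampling it says "The study will be conducted in a convenience sample recruited at rheumatology, dermatology, other specialist and primary care practices" and "Patients will be recruited on a consecutive basis".

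Section 8.3 counts evaluable patients by type of recruiting site, 400:400:200 for rheumatology, dermatology and neither. It states: "With 400 evaluable patients in rheum and dermatology sites, the study has 90% power to detect a difference in means between the two specialties". The test behind this claim is a two-sample t-test at the 5% level, and the assumed effect size is 0.229. A parallel statement gives 90% power at 0.281 when either of the first two groups is compared with the third. The only inflation of the sample is for diagnoses that are not confirmed. Number of sites, patients per site, intraclass correlation and design effect are not mentioned.

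Section 8.2 plans mean differences or odds ratios with 95% confidence intervals from simple and multiple regression: "Depending on the scale of the dependent variable, linear or logistic models will be used". It does not say how site or country will be handled. It refers to a separate SAP, and the item it expressly leaves to that SAP is the definition of the analysis populations.

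**The concern.** Every patient recruited at a practice has the same value of the exposure, because the exposure is the type of practice. Differences between practices in how fast they diagnose, refer or start a csDMARD or bDMARD therefore cannot be separated from specialty within a site. They enter the variance of the specialty contrast in full. A t-test on 400 and 400 independent patients leaves this component out.

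If outcomes are positively correlated within sites, the direction of the error is fixed: true power is below the stated 90%. Any confidence interval computed as if patients were independent would also be too narrow. At stake are the precision offered in support of about 1200 patients and the coverage of the intervals for the primary association.

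**Working it through.** **Inputs from the protocol (8.3):** 400:400 at effect size 0.229; 400:200 at 0.281; significance level 5%; power 90%. Sidedness is not stated; a one-sided test would give 94.4% for the first comparison, so the calculation must be two-sided.

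**Reproducing the stated figures (independence, SD = 1):** power = Φ(d / √(1/n₁ + 1/n₂) − 1.96).

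- 400:400: 0.229 / √(2/400) = 3.239; Φ(3.239 − 1.960) = 89.9% (noncentral t also 89.9%).
- 400:200: 0.281 / √(1/400 + 1/200) = 3.245; Φ(3.245 − 1.960) = 90.1% (noncentral t 90.0%).

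The recruitment figures also hold: 450 × 0.90 = 405, 480 × 0.85 = 408 and 270 × 0.75 = 202.5 evaluable. The arithmetic of 8.3 is therefore correct, and the allowance for unconfirmed diagnosis leaves no meaningful reserve for clustering.

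**Adding site clustering:** DE = 1 + (m − 1) × ICC, with m evaluable patients per site.

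- Power = Φ(d / √(DE × (1/n₁ + 1/n₂)) − 1.96).
- Effect detectable with 90% power = stated effect × √DE.
- True coverage of a 95% interval that ignores site = 2Φ(1.96/√DE) − 1.

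Worked case, m = 10 and ICC = 0.05: DE = 1 + 9 × 0.05 = 1.45 and √DE = 1.204. Power at 0.229 = Φ(3.239/1.204 − 1.960) = 76.7%. Detectable effects are 0.229 × 1.204 = 0.276 and 0.281 × 1.204 = 0.338. Coverage = 2Φ(1.960/1.204) − 1 = 89.6%. Effective size is 400/1.45 = 276 per group of 400.

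**Range.** Both m and ICC are assumptions, since the protocol gives neither. Equal m across sites and a normal approximation are used.

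| m | ICC | DE | Power at 0.229 | Power at 0.281 | Detectable, 400:400 | Detectable, 400:200 | Coverage if site ignored |
|---|---|---|---|---|---|---|---|
| 5 | 0.01 | 1.04 | 88.8% | 88.9% | 0.234 | 0.287 | 94.5% |
| 5 | 0.05 | 1.20 | 84.0% | 84.2% | 0.251 | 0.308 | 92.6% |
| 5 | 0.10 | 1.40 | 78.1% | 78.3% | 0.271 | 0.332 | 90.2% |
| 10 | 0.01 | 1.09 | 87.3% | 87.4% | 0.239 | 0.293 | 94.0% |
| 10 | 0.05 | 1.45 | 76.7% | 76.9% | 0.276 | 0.338 | 89.6% |
| 10 | 0.10 | 1.90 | 65.2% | 65.3% | 0.316 | 0.387 | 84.5% |
| 20 | 0.01 | 1.19 | 84.3% | 84.5% | 0.250 | 0.307 | 92.8% |
| 20 | 0.05 | 1.95 | 64.0% | 64.2% | 0.320 | 0.392 | 84.0% |
| 20 | 0.10 | 2.90 | 47.7% | 47.8% | 0.390 | 0.479 | 75.0% |

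The stated 90% corresponds to DE = 1, that is, ICC = 0 or one patient per site.

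**The case against.** **The SAP may deal with it.** Random effects and clustered standard errors fit within linear or logistic regression and are often left to the SAP, which is not at hand. A reader might infer from section 8.2 that the reported intervals will under-cover and produce false specialty differences. The protocol does not support that. It is silent on site handling and does not commit to independence-based standard errors. The coverage figures therefore apply only if the named models are fitted without allowing for site. The power statement is different: it is fixed in 8.3, and a later analysis model cannot make it true.

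**The study is exploratory.** Section 8.3 says there is no basis for judging the effect size and calls the objectives non-confirmatory. The values 0.229 and 0.281 look like what 400:400:200 can detect, not clinically motivated targets, and no decision rule depends on the 90%. This stands and lowers the severity, but it does not make the stated power correct.

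**The size is assumed.** This also stands. With few patients per site and a low ICC the loss is one or two points. The worst row fits the third group poorly: 200 evaluable patients at 20 per site means 10 sites, fewer than the roughly 15 countries planned. It is not excluded, since cluster size may differ by specialty, but it should not drive the judgement.

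**Country.** A reader might infer that all between-country variation falls into the specialty contrast, or that country confounds it because care shares differ between countries. Neither is shown. Section 6.1.2 wants sites broadly representative of care settings within each country, which points to specialty being at least partly crossed with country. The shares in 6.1 come from a cited survey of care, not a recruitment plan, and vary little (for example 37–38% for rheumatology and 22–28% for dermatology).

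**Conclusion.** The concern holds for the power statement in section 8.3. The 90% reproduces only under independence, and specialty varies only between sites, so for any positive within-site correlation the design has less power than stated. Positive correlation is plausible because times to diagnosis and to first csDMARD or bDMARD reflect local referral and prescribing, but the protocol gives no estimate of it.

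Over assumed values of 5 to 20 patients per site and ICC 0.01 to 0.10, power at 0.229 runs from 88.8% down to 47.7%, and power at 0.281 is within 0.2 points of that. The interval half of the point is conditional: coverage of about 94.5% down to 75% applies if site is ignored in the section 8.2 models. Claims of country confounding, or of certain under-coverage in the final analysis, go beyond the document.

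This should be fixed, but it does not invalidate the study: the objectives are exploratory and the size of the loss is unknown.

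**What to change.** 1. In section 8.3, give the planned number of evaluable patients per site and a range of ICC. Restate the effects detectable with 90% power as 0.229 × √DE and 0.281 × √DE, with DE = 1 + (m − 1) × ICC. Alternatively, remove the 90% claim. No patients need be added.
2. In section 8.2, or in the SAP with a reference from 8.2, fit all models for specialty with a site random effect or with standard errors clustered by site, and include country as a covariate.

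The cost is wording, wider intervals and a less favourable power statement. The change also requires that site and country can be traced from each patient number. Section 7 says the forms carry a unique patient number and go to the affiliate office of the country, which suggests that they can. However, no site or country field is listed among the recorded items, so this should be confirmed.

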A number of international and national recommendations for the management of PsA and corresponding treatment algorithms have been published in the past few years in both rheumatology and dermatology (28-31, 34, 35). Ideally, management of PsA should address joints and skin as well as extra-articular manifestations and comorbidities (34, 35). It has been demonstrated that PsA patients receiving a multidisciplinary care, involving both rheumatologists and dermatologists in a US clinic, were more likely to receive systemic medication (25% vs 15%) and be treated with a biologic agent (37% vs 16%) than in prior unidisciplinary care (36).

While consensus is evident among the recommendations on the main treatment principles, the extent to which they are followed by practicing physicians is unknown. In reality it appears that many patients with PsA are not diagnosed, or are undertreated or not treated systematically (34, 37). A recent large population based multinational survey conducted in North America and Europe revealed that approximately 15% of patients with PsA had not seen a health care provider in the past year, and almost 60% were not being treated for their joint disease (38).

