## 8. Data Analysis Plan

### 8.1. Endpoints

#### Primary Endpoints

- Time from inflammatory musculoskeletal symptom onset to PsA diagnosis
- Time from PsA diagnosis to first csDMARD
- Time from PsA diagnosis to first bDMARD
- Time from first csDMARD to first bDMARD

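### Section 8.3's 90% power can hold in full at most for onset-to-diagnosis; the three DMARD endpoints use only treated patients, so their power is lower by an amount the protocol does not state

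*Protocol*

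**What the plan says.** Section 8.3 makes two power statements. The first reads "With 400 evaluable patients in rheum and dermatology sites, the study has 90% power to detect a difference in means between the two specialties", and continues "with a two-sample t-test at a significance level of 5% assuming an effect size of 0.229". The second starts "With 400 evaluable patients in rheum or dermatology sites and 200 evaluable patients in non-rheum/non-dermatology sites" and gives 90% power for either specialty against the third group, "with a two-sample t-test at a significance level of 5% assuming an effect size of 0.281". Neither names an endpoint.

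The section then inflates recruitment for non-confirmed PsA only (10%, 15% and 25% by setting), which gives about 1200 patients (450:480:270), "in order to achieve 1000 evaluable patients (400:400:200 in rheum:dermatology:non-dermatology/non-rheum, respectively"). It also says that there is no basis for judging the effect size and that the study is exploratory.

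Section 8.1 lists four primary endpoints. One is time from symptom onset to diagnosis. The other three are diagnosis to first csDMARD, diagnosis to first bDMARD ("Time from PsA diagnosis to first bDMARD"), and first csDMARD to first bDMARD.

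Section 8.2 makes confirmed PsA the condition for analysis. It plans mean differences or odds ratios from linear or logistic models and leaves the exact analysis populations to a separate SAP. It names no method for censored times. The study is cross-sectional (Section 6.1).

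**The concern.** The 400/400/200 base counts every patient with confirmed PsA. A time to first csDMARD or bDMARD exists as an observed number only for a patient who has started that drug, and the csDMARD-to-bDMARD interval needs both. In a cross-sectional study, a patient untreated at the visit never acquires a start date. Under the test that Section 8.3 itself names, the sample for these three endpoints is therefore the treated subset, and nothing in the section allows for that.

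The primary objective covers the management steps as well as diagnosis. A reader of Section 8.3 will take the 90% to cover all four primary endpoints, and could give an inconclusive specialty comparison for biologics more weight than the number of treated patients supports.

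**Working it through.** **Inputs from the protocol.** From Section 8.3: 400, 400 and 200 evaluable patients; d = 0.229 and 0.281; 5% significance level (taken as two-sided, which reproduces the stated power); losses of 10%, 15% and 25%.

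**Step 1: the plan's own figures.** For a two-sample t-test the noncentrality is λ = d / √(1/n₁ + 1/n₂), and power comes from the noncentral t distribution.

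- 400 vs 400: λ = 0.229 / √(2/400) = 3.239, power 89.9%.
- 400 vs 200: λ = 0.281 / √(1/400 + 1/200) = 3.245, power 90.0%.
- Recruitment, n/(1 − loss): 400/0.90 = 445, 400/0.85 = 471, 200/0.75 = 267 (rounded up). The plan's 450, 480 and 270 yield 405, 408 and 202.5 expected evaluable patients.

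Both power figures and the recruitment target reproduce.

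**Step 2: only a share f has a value.** With f equal in all settings, the groups become 400f, 400f and 200f. λ is multiplied by √f, and the difference detectable with 90% power grows roughly as 1/√f. For f = 40%: λ = 3.239 × √0.40 = 2.048, power 53%.

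The protocol gives no uptake for its own sample, so f is an assumption. The range below uses the Introduction's background figures and two higher values:

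- 7.6% and 37%: bDMARD use in the standard-care and tight-control arms of a trial in early PsA.
- 16% and 37%: a US clinic, where patients under multidisciplinary care were more likely to "be treated with a biologic agent (37% vs 16%) than in prior unidisciplinary care".
- 40%: the complement of the survey finding that "almost 60% were not being treated for their joint disease".
- 60% and 80%: assumed, to allow for wider ever-use of csDMARDs.

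| Share with a value | n per setting | Power at 0.229 (1:1) or 0.281 (2:1) | Detectable d at 90% power, 1:1 / 2:1 |
|---|---|---|---|
| 100% | 400/400/200 | 90% | 0.23 / 0.28 |
| 80% | 320/320/160 | 82% | 0.26 / 0.31 |
| 60% | 240/240/120 | 71% | 0.30 / 0.36 |
| 40% | 160/160/80 | 53% | 0.36 / 0.45 |
| 37% | 148/148/74 | 50% | 0.38 / 0.46 |
| 16% | 64/64/32 | 25% | 0.58 / 0.71 |
| 7.6% | about 30/30/15 | 14% | not tabulated |

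About 75% of confirmed patients would need a value for power to reach even 80%.

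**Step 3: unequal uptake.** If 37% of rheumatology and 16% of dermatology patients have a value (148 vs 64), λ = 0.229 / √(1/148 + 1/64) = 1.531 and power is 33%. This is an illustration only.

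**The case against.** The strongest reply is that Section 8.3 is true as written. It is conditional on the evaluable numbers and effect sizes, it names no endpoint, and its arithmetic reproduces. The study is declared exploratory, effects are to be reported with 95% confidence intervals, and the SAP may define how untreated patients are handled. All of that stands, and it limits the consequence to lower precision on three of the four primary endpoints, not a failed confirmatory test. It does not rescue the 90%. If untreated patients are kept as censored, power depends on the number of starts. If the endpoint is made yes/no for a logistic model, a difference in means no longer applies. In neither case is a t-test on 400/400/200 the relevant calculation.

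A reader might infer that power for the DMARD endpoints is 25% to 53%, as 16% to 40% uptake would give. The documents do not establish that:

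- The uptake figures describe other populations. The survey included about 15% of patients who had seen no provider in the past year, whereas this study enrols patients at routine visits.
- The survey figure describes patients being treated at the time, whereas a first csDMARD depends on ever-use. Ever-use could be well above 40%.
- Power could also fall below 25%: 7.6% uptake gives 14%, and the csDMARD-to-bDMARD interval needs both drugs.

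A reader might also want to deduct missed consulting visits. The protocol gives no rate for them. Symptoms, diagnosis and treatment are recorded at the recruiting site in Module 1 (Section 6.3), so a missed visit need not remove a primary-endpoint value.

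**Conclusion.** The point holds in a conditional form. The 90% at 0.229 and 0.281 can apply in full at most to time from symptom onset to diagnosis, and only if onset dates are complete. For the three DMARD endpoints, analysed as observed times, power is below 90% whenever some confirmed patients have not started the drug. The protocol's own background makes that close to certain for biologics.

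The size of the shortfall is not fixed by the documents. Over the assumed shares of 7.6% to 80%, equal across settings, power runs from 14% to 82%. The fault is a power statement not tied to an endpoint, not an error of calculation. It should be corrected, but it does not call the design into question.

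**What to change.** In Section 8.3:

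- State that the 90% power at 0.229 and 0.281 refers to time from symptom onset to diagnosis.
- For each of the three DMARD endpoints, state the number of patients per setting assumed to have a value, with the source of that assumption, and the resulting detectable difference.
- If untreated patients are to be analysed as censored, give instead the detectable hazard ratio at the expected number of starts.

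The cost is one paragraph and less favourable stated figures. No enlargement, design change or added data collection is needed.
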